### Prototype Development

Insights from both the MIRT- and MODN-based approaches will inform final prototype design, including the possibility of hybrid architectures that combine strengths of probabilistic prediction and latent severity estimation. Two complementary user interfaces will be developed to reflect the different contexts in which AfriCAT may be used within measurement-based mental health care systems.

The first is an adolescent-facing interface designed for self-administration, for example, via smartphone or tablet in school, community, or clinic settings. This version will deliver symptom questions adaptively, presenting items sequentially based on prior responses to minimize burden while maintaining precision. Upon completion, the tool will provide structured feedback tailored to symptom severity alongside guidance regarding appropriate referral or support options.

The second interface is a provider-facing version intended for use by primary health care workers, mental health professionals, or trained lay providers within task-shared systems of care. In this format, the adaptive assessment will be designed for integration into the clinical encounter, supporting real-time evaluation of symptom severity. The tool will be designed to generate dimensional severity estimates and probabilistic diagnostic outputs that can inform clinical decision-making. The prototypes developed during this study are intended for research and feasibility testing only and will not be used to make independent clinical decisions or provide automated crisis management recommendations.

### Participatory Workshops

Participatory workshops will ensure that AfriCAT is grounded in the perspectives and priorities of young people and that the resulting prototypes are acceptable, comprehensible, and contextually appropriate. A total of four participatory workshops will be conducted in Nairobi, Kenya, and Agincourt, South Africa (two in each country). During these workshops, approximately 50 young people aged 10 to 24 years will engage in focus group discussions, guided by semistructured interview guides (Multimedia Appendix 1).

The first workshops will explore the acceptability of adaptive assessment approaches, including perceptions of dynamically changing questions and the tone and framing of feedback provided by the tool. Adolescents will also be invited to reflect on privacy expectations, data-sharing concerns, and preferences regarding who should have access to their assessment results. In addition, discussions will examine preferred implementation contexts, such as schools, clinics, universities, or home-based digital platforms. The final workshops will involve prototype testing, completion of validated feasibility and acceptability quantitative surveys (Multimedia Appendix 1), and a focus group discussion to further unpack adolescents’ perceptions of the AfriCAT tool and reflect on their experiences of involvement in the co-design process.

### DCE

To complement qualitative data, a DCE will be conducted to quantify adolescent preferences regarding key design and implementation features of AfriCAT. A total of 500 adolescents aged 12 to 24 years will be recruited from schools, communities, and universities across Kenya and South Africa. The DCE will focus on five attributes considered central to tool design: (1) where the test can be taken (access pathway), (2) how questions about personal information are handled (privacy of demographics), (3) who can see the results (results sharing), (4) how much and what information appears on the results page, and (5) the description of the tool on the landing page. Each attribute will be presented at 2 or 3 levels, described in simple language familiar to adolescents (Multimedia Appendix 1).

In total, 20 choice tasks will be created, each consisting of 2 alternative versions of the tool that differ in how the attributes are combined. Participants will be presented with a series of hypothetical scenarios in which alternative versions of AfriCAT differ across these attributes. For each pair of scenarios, adolescents will indicate their preferred option. This approach allows estimation of the relative importance placed on different features and the trade-offs adolescents are willing to make between them. To minimize burden and reduce fatigue, these tasks will be divided into 2 blocks of 10 tasks each. Participants will be randomly assigned to group A or group B, with each group completing one block (10 tasks). Within each task, participants will be asked to select which of the 2 versions they would prefer to use. Randomization ensures that participants are evenly distributed across the 2 blocks, while still allowing researchers to collect sufficient data for robust analysis. The DCE design will follow best practice principles of experimental design, using a D-efficient approach to maximize the information gained from each participant’s choices. Dominance checks and attention filters will be included to monitor data quality.

Choice modeling techniques, such as conditional or mixed logit models, will be used to estimate preference weights and to examine whether preferences vary by age group, gender, or country. Findings from the DCE will inform refinement of the prototypes and support implementation strategies that align with adolescent priorities.

### Stakeholder Interviews

To complement adolescent perspectives, approximately 20 to 24 semistructured interviews will be conducted with mental health providers, primary health care workers, and policymakers in Kenya and South Africa following a semistructured interview guide (Multimedia Appendix 1). These interviews will explore how AfriCAT could be integrated into existing health and education systems, with particular attention to feasibility within resource-constrained environments. Discussions will examine alignment with stepped-care protocols, potential roles within task-shared service models, evidence requirements for broader adoption or policy endorsement, and perceived resource implications, including workforce and training considerations. Insights generated through this process will inform the development of an implementation strategy and ensure that AfriCAT is responsive not only to adolescent preferences but also to system-level realities.

### Ethical Considerations

Ethical approval for the AfriCAT study has been obtained from the Human Research Ethics Committee (Medical) at the University of the Witwatersrand (MED 25-06-1023) and the Aga Khan University Institutional Review Board (2025/ISERC-147). The study will be conducted in accordance with the Declaration of Helsinki and relevant data protection legislation in South Africa and Kenya. The secondary data analysis component uses deidentified individual-level data from K-NAMHS, and no attempts will be made to reidentify participants. Data will be stored securely on institutional servers, with access restricted to authorized study personnel and managed in compliance with applicable data protection policies.

The participatory components involve adolescents who self-identify as having lived experience of depression and/or anxiety and are therefore considered a vulnerable group. Adolescents aged 13 to 17 years will provide written assent and parental consent, while participants aged 18 years and older will provide written informed consent. Information sheets will emphasize the voluntary nature of participation, the right to withdraw at any time, and the absence of consequences for nonparticipation. A study-specific distress protocol (Multimedia Appendix 1) has been developed to guide the identification and management of participant distress.

Participants who disclose suicidal ideation, significant psychological distress, risk of harm to self or others, abuse, or other safeguarding concerns during study activities will be managed according to the study-specific distress protocol. Facilitators conducting workshops, interviews, and prototype testing will be trained in recognizing and responding to participant distress. Where immediate risk is identified, participants will be referred to appropriate local mental health, social, or emergency services in accordance with site-specific referral pathways. For participants younger than 18 years, parental or guardian involvement will occur where required for participant safety and in accordance with local ethical requirements and applicable laws. Workshops and interviews will be facilitated by trained researchers, including team members with clinical experience in adolescent mental health.

Confidentiality will be strictly maintained through the use of unique study identification numbers and secure storage of identifiable information separate from research data. Audio recordings will be deidentified during transcription and deleted once accuracy is verified. Although confidentiality within focus group discussions cannot be fully guaranteed, participants will be informed of these limitations and encouraged to respect the privacy of others. Participants will be informed that confidentiality may be breached where there is concern regarding imminent risk of serious harm to themselves or others, or where disclosure is required by law or ethical obligations relating to child protection. The AfriCAT prototypes will not be deployed clinically during this phase of research; any future implementation or large-scale use will undergo additional ethical review.

### Outcomes

#### Primary Outcomes

Because MIRT and MODN estimate fundamentally different quantities, namely severity and probability of diagnosis, they cannot be meaningfully compared head-to-head. Instead, we will review the relative strengths and limitations of the models in supporting measurement-based mental health care. Primary metrics of evaluation will include (1) precision of severity estimation across internalizing symptom dimensions; (2) efficiency, operationalized as the median number of items required to achieve stable estimates or certain predictive performance; and (3) diagnostic classification performance relative to *DSM-5* diagnoses for MDD, GAD, SoPh, and PTSD. Diagnostic classification performance will be evaluated using established metrics such as sensitivity, specificity, and area under the receiver operating characteristic curve. To assess fairness across age and gender, each outcome will be computed for each subgroup and compared.

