### Study Aim and Objectives

The overall aim of the AfriCAT study is to develop and internally validate a computerized adaptive assessment for adolescent depression and anxiety designed to support measurement-based mental health care in African contexts. Specific objectives are as follows:

to develop and calibrate adaptive assessment models for depression and anxiety using nationally representative adolescent mental health survey data.to evaluate the precision, efficiency, and diagnostic classification performance of the adaptive assessment through simulation-based internal validation.to compare adaptive algorithms derived from multidimensional item response theory (MIRT) and modular clinical decision support network (MODN) architectures.to incorporate adolescent perspectives through participatory workshops and discrete choice experiments (DCEs) to inform tool design and implementation.to assess stakeholder perspectives regarding the feasibility and potential integration of adaptive assessment into existing mental health systems.

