### MIRT-Based CAT Development

To capture the latent structure of symptoms appropriately, a bifactor multidimensional framework is outright adopted for model calibration. Within this definitive framework, all items load directly onto a single general internalizing factor while simultaneously contributing to independent, disorder-specific factors corresponding to MDD, GAD, SoPh, and PTSD. Model fit for this bifactor configuration will be rigorously assessed by evaluating the strength and significance of item factor loadings, examining global fit statistics, specifically the limited-information M2 statistic alongside absolute and relative indices such as the root mean square error of approximation and the comparative fit index, and visually inspecting observed versus expected item response plots to identify localized areas of measurement.

*DISC-5* symptom items in the K-NAMHS dataset are recorded as binary (yes/no) responses, indicating the presence or absence of specific symptoms. Item parameters will therefore be estimated using dichotomous item response theory models, allowing estimation of item discrimination and severity parameters for each symptom indicator. The baseline MIRT bifactor calibration will be executed via a stochastic expectation-maximization algorithm. To ensure population representativeness, normalized complex survey weights will be integrated directly into the estimation process to scale individual contributions to the marginal likelihood. Missing data handling strategies will differ by analytical phase. For the core MIRT calibration, missingness will be accommodated via full-information maximum likelihood, which leverages all available structural information without data loss. However, because post hoc adaptive testing simulations within the MIRT-CAT framework require a complete matrix to execute through high-missingness skip patterns, model-based plausible value imputation will be utilized strictly to construct the complete simulation response bank.

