### MODN

In parallel with the MIRT-based development, AfriCAT will also be implemented using a MODN architecture [27]. MODN is a modular neural network framework in which each symptom question functions as an independent module that updates diagnostic probability estimates sequentially as new information is obtained [27]. Rather than estimating a single latent trait, this approach models the evolving probability of specific diagnostic states, recalibrating predictions dynamically with each response. Unlike traditional latent trait models, MODN more closely mirrors the logic of a clinical consultation, in which information is gathered iteratively and diagnostic impressions are updated in real time.

A deep learning encoder module will be created for each question in the dataset. A deep learning decoder module will be created for each outcome. Missing data are accommodated by the modular architecture and are simply ignored.

Five-fold cross-validation will be performed on the training set to optimize the hyperparameters of the models. The final models will then be trained on the full training set with the optimal hyperparameters. All analyses will be performed using the trained models on the test set. Overfitting will be controlled by early stopping the training after increases in the validation loss and sanity-checking the loss curves.

To remedy the low prevalence of internalizing disorders, we will also train models that overweight positive diagnosis cases. As the survey weights do not substantially alter the prevalence of the internalizing disorders, the models trained using them are not expected to differ significantly and would be less representative of individual adolescents. We will therefore not use the survey weights.

The model achieving the best prediction performance using all the questions on the test set will then be selected. Different combinations of next-question-selection methods and stopping rules will be compared based on their predictive performance and efficiency. They will be compared against baselines using entropy-based methods as next-question-selection and the *DISC-5* diagnostic criteria satisfaction as the stopping rule.

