## Discussion

### Expected Outcomes

The primary expected outcome of AfriCAT is the development and internal validation of a computerized adaptive assessment for adolescent depression and anxiety calibrated using nationally representative Kenyan adolescent mental health data. Subsequent research will evaluate the transportability and performance of the adaptive assessment in other African settings. The study will generate new knowledge regarding the dimensional structure of internalizing symptoms in Kenyan adolescents, the feasibility of adaptive assessment within this context, and the comparative performance of MIRT-based and modular neural architectures for mental health evaluation. By integrating psychometric modeling with participatory co-design and quantified preference elicitation, the study will also contribute methodologically to the emerging field of digital mental health in LMICs.

Beyond advancing psychometric science, AfriCAT is intended to serve as foundational infrastructure for measurement-based adolescent mental health care. The adaptive engine is designed to support identification of clinically significant symptoms, stratification within stepped-care models, and longitudinal monitoring of treatment response. In resource-constrained systems, where specialist capacity is limited and task-shared models are required, efficient and precise assessment tools are essential for optimizing allocation of care. By reducing assessment burden while maintaining measurement precision, AfriCAT has the potential to support scalable screening and monitoring without overwhelming services.

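### The plan sets out to compare MIRT with MODN, then rules out a head-to-head comparison for a reason that does not cover its own diagnostic classification metric

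*Protocol article*

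**What the plan says.** Study Aim and Objectives lists as the third objective "to compare adaptive algorithms derived from multidimensional item response theory (MIRT) and modular clinical decision support network (MODN) architectures". Under Expected Outcomes, the discussion says the study will produce new knowledge on "the comparative performance of MIRT-based and modular neural architectures for mental health evaluation". The Strengths section counts the ability to compare the two architectures as a strength.

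Primary Outcomes takes the opposite line: "Because MIRT and MODN estimate fundamentally different quantities, namely severity and probability of diagnosis, they cannot be meaningfully compared head-to-head". The next sentence gives the substitute: "Instead, we will review the relative strengths and limitations of the models in supporting measurement-based mental health care". The same paragraph then names three primary metrics:

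- The first concerns severity and is given as "precision of severity estimation across internalizing symptom dimensions".
- The second concerns test length and is worded so as to cover both engines: "efficiency, operationalized as the median number of items required to achieve stable estimates or certain predictive performance".
- The third is classification against DSM-5 diagnoses of MDD, GAD, SoPh and PTSD, measured by sensitivity, specificity and AUC. Nothing there limits this metric to one engine.

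On evaluation data, MIRT-Based CAT Development runs its post hoc simulations over all calibrated records. The MODN section carries out all its analyses on the test set. The Analysis section defines that set as a held-out 20%, stratified on the outcomes, without naming an engine.

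**The concern.** A listed objective and a promised result conflict with the section that defines the primary outcomes. The article itself takes both positions, so this is not detail that a condensed article leaves to a fuller plan.

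The ground for refusing the comparison is that one engine estimates severity and the other the probability of a diagnosis. That is a statement about outputs. It does not settle whether the two can be judged against a common reference standard, and the third metric supplies one.

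At stake is whether the study can say which engine classifies better, by how much and with what uncertainty. As written it would publish two sets of classification figures, state no criterion for weighing them, and draw them from different records. Readers will set the AUCs side by side regardless, and any gap would mix the engine with the difference between in-sample and held-out scoring.

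**Working it through.** The plan gives no figure to reproduce for this point. The check sets the sections side by side and takes the metrics one at a time.

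**Step 1: does the stated reason apply to each primary metric?**

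- *Severity precision.* This is defined for MIRT, which yields trait estimates with standard errors. MODN is described as modelling diagnostic probabilities rather than a latent trait. The reason holds.
- *Median number of items.* This can be counted for both, but the definition joins two end points with an *or*: stability of the estimate, or a level of predictive performance. MIRT stops on the standard error of the general factor or at a question cap, not on any one disorder. Item count therefore applies to both engines but is not like-for-like as written.
- *Diagnostic classification.* The reference is the same four diagnoses in the same adolescents. AUC needs only a score that ranks people, so a trait score serves as well as a probability. Sensitivity and specificity also need a cut-off, which can be set for either score. The reason does not hold.

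Tally: one metric specific to MIRT, one shared but with unequal end points, and one shared on a common scale.

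**Step 2: would the shared metric be comparable as planned?**

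- MIRT is scored on all calibrated records, and so on records that helped to estimate its item parameters. If *calibrated* were read to mean only the 80% training set, the scoring would still be in-sample.
- MODN is scored on the held-out 20%.

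On either reading the engines are scored on different records, one in-sample and the other held out. The size of the resulting distortion cannot be derived from the document, and none is claimed here.

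**Step 3: how much information would a common test set carry?**

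- Survey sample: 5155 pairs (Data Source). Test share: 20% (Analysis).
- Test records: 0.20 × 5155 = 1031. Training records: 5155 − 1031 = 4124.
- The MODN section calls prevalence low but gives no figure. Assuming 1% to 5% per disorder, cases in the test set would number 0.01 × 1031 ≈ 10 to 0.05 × 1031 ≈ 52.

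A paired comparison is feasible, but with so few cases per disorder the differences will be imprecise. They should be read as estimates with intervals rather than as tests.

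**The case against.** The best defence is that the objective is narrowed, not dropped. Primary Outcomes rules out only a head-to-head comparison and replaces it with a review alongside quantitative metrics. The objective does not promise a paired performance analysis, and Study Design calls the two approaches complementary. On this view only the Expected Outcomes sentence is in direct conflict, and rewording would cure it. Much of this stands. A reader might infer that the third objective cannot be answered at all; the documents do not support that. What is left without a planned answer is comparative performance.

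Three other strong readings also fail.

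- *The prototype will be chosen from non-comparable numbers.* Prototype Development says insights from both approaches will inform the design, possibly as a hybrid. It gives no rule that picks an engine by score.
- *The two sets of results describe different target populations.* For MIRT, "normalized complex survey weights will be integrated directly into the estimation process"; for MODN, "We will therefore not use the survey weights". Both statements concern model fitting. No section says that the MIRT performance metrics are weighted, and the MODN section states that weighting barely changes prevalence.
- *The distortion can be put at a given number of AUC points.* Nothing in the document supports such a figure.

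It is also fair to say that the Analysis section states the split in general terms, so the authors may intend it for MIRT too. The MIRT section nevertheless says otherwise, and the two need reconciling. Finally, the authors' caution has some basis: like-for-like figures require matched item counts and a defined MIRT score per disorder. That is a reason to specify the comparison, not to call it meaningless.

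**Conclusion.** The point holds in a limited form. One of the five objectives, together with the Expected Outcomes and Strengths sections, promises a comparison that Primary Outcomes reduces to a narrative review without a criterion. The justification is sound for severity precision, and likewise for calibration of probabilities (a MODN-only secondary outcome). It is unsound for diagnostic classification, and item count would need a common end point. Separately, the mismatch in evaluation records would make the classification figures non-comparable even if they were set side by side.

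The contradiction and the mismatch rest on the text alone. Only the range of about 10 to 52 test-set cases per disorder depends on an assumption, namely prevalence of 1% to 5%. According to the Results section the simulation-based validation is still to come, so this can be settled before any performance figures are seen.

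**What to change.** In Primary Outcomes, confine the statement that the engines cannot be compared to severity precision and probability calibration, and keep those as engine-specific outcomes. Then add text along these lines:

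> Diagnostic classification by the two engines will be compared on the same held-out test records, with MIRT calibrated on the training set only. For each of the four disorders we will report the paired difference in AUC, with a confidence interval, at matched numbers of administered items. These differences are estimates; given the few cases per disorder they are expected to be imprecise.

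The text should say which MIRT score ranks adolescents for each disorder; a logistic combination of the general and disorder-specific scores, fitted in the training set, would do. MIRT-Based CAT Development should be brought into line with the split in the Analysis section. For the comparison to be fair, tuning on both sides should be finished within the training set. That includes the MIRT precision threshold and the choice among MODN models, which the MODN section currently makes on the test set.

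The cost is one MIRT recalibration on the 80% training set (4124 records) and rerunning or redirecting simulations that have not yet been done. No new data are needed. A calibration on all records can still be kept for the final item parameters.

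If the sponsor does not want this comparison, the alternative is to reword the third objective, Expected Outcomes and Strengths as a descriptive review of the two approaches. That costs only an edit, but gives up the comparative performance result.
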